## Background

Muscle soreness after exercise, known as delayed-onset muscle soreness (DOMS), occurs after long-term physical activity or unusual exercise [1, 2]. DOMS symptoms, such as pain, discomfort, muscle tenderness, or loss of range of motion, usually occur 12–48 h after exercise and mend within 7 days. DOMS symptoms occur when structural damage to the muscle fibers initiates an inflammatory reaction cascade, which consequently increases inflammatory markers and intramuscular enzymes, such as creatine kinase (CK) [2, 3]. However, the mechanism of DOMS after exercise has not been fully elucidated. Although symptoms disappear over time, eccentric activity may cause significant changes to muscle function and may increase the risk of sports injuries [2]. Analgesics can be used for severe pain, but some studies have demonstrated a lack of efficacy of non-steroidal anti-inflammatory drug treatments [4, 5]. Many studies have attempted to identify ways to alleviate DOMS symptoms, such as massage, cryotherapy, cold-water immersion, and laser acupuncture [6–11]. Various supplements with anti-inflammatory and antioxidant effects have been studied to help recovery after exercise [12–14]. Moreover, there has been increasing interest in herbal medicines to treat DOMS because of their holistic approach and minimal side effects [15].

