### Study design

This study will be a randomized, placebo-controlled, crossover design, investigator-initiated clinical trial. The trial will be conducted at Pusan National University Korean Medicine Hospital. Thirty healthy male adults will be recruited via hospital bulletin boards and local advertisements. Subjects who voluntarily wish to participate in this study and provide written informed consent will undergo a screening assessment to determine their eligibility. Subjects will be hospitalized for 4 days. On the first day, the subjects will perform eccentric exercise for 1 h to induce DOMS. After exercise, the subjects will be administered either JGT or placebo for 3 days. After a more than 1 week wash-out period, the subjects will repeat the same process with the other drug. The duration of the wash-out period was calculated based on the major component of JGT with the longest half-life. As glycycoumarin has the longest half-life (*T*_1/2_) of 14.9 h [20], we decided that the wash-out period should be 6.21 days or more, which is 10 times the half-life of glycoumarin needed to minimize the carry-over effect of JGT. The overall study flow is shown in Fig. 1. A detailed schedule is given in Fig. 2 and Table 1.

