### Sample size

As no clinical trial has evaluated the efficacy of JGT on DOMS, a sample size calculation was impossible. A study estimating the sample size for a pilot study proposed 15 subjects per treatment arm as an optimal sample size for the standardized effect size with 90% power and two-sided 5% significance [8].

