### Statistical analysis

The statistical analysis will be conducted by an independent statistician using SAS version 9.4 (SAS Institute). The significance level will be set at 0.05 in a two-tailed test. All continuous data will be presented as means and 95% confidence intervals (CIs). Categorical data will be reported as frequencies and percentages. The intention-to-treat (ITT) principle will be applied for the primary analysis. The ITT population will include subjects who meet the full analysis set (FAS) criteria, including subjects who had the primary outcomes assessed once or more except for the baseline measures and who took the test drug at least once. Subjects who do not meet the eligibility criteria, those who did not take the test drug throughout the study, and those who have never been evaluated after the screening visit will be excluded from the FAS dataset. The per-protocol set will also be analyzed, which will only include subjects who have completed the study as a supplementary analysis.

The baseline characteristics of the study subjects will be presented using a descriptive analysis for each group. The primary outcome will be the differences between the VAS score with motion measured at various intervals from 0 to 72 h after exercise. A mixed-effect model for repeated measures (MMRM) will be used to assess differences along with the time effect. The dependent variable will be the change in the VAS score (pain with motion) measured from 0 to 72 h after exercise. The model will include treatment and protocol-specified visits as fixed effects, and subjects as a random factor. Dunnett’s test will be used for multiple comparisons. The results of the secondary effective analysis will be analyzed using the same method as for the primary outcome, in the case of continuous variables with time variation. Additionally, Student’s *t* test or Wilcoxon’s signed-rank test will be used to compare results before and after the treatment within each group. Categorical data will be analyzed using the chi-squared test or Fisher’s exact test. Missing values by maximum likelihood will be considered when the MMRM is used. The last observation carried forward method will be adopted for missing values for Student’s paired *t* test, the Wilcoxon signed-rank test, or repeated measures analysis of variance.

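### The supplementary before/after tests within each drug cannot show a drug effect, and carrying the last score forward contradicts the protocol's own course of soreness; the primary mixed model is not affected

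*Protocol article*

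**What the plan says.** All of the analysis rules are in the protocol article, section Statistical analysis.

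- Primary outcome (VAS with motion): "A mixed-effect model for repeated measures (MMRM) will be used to assess differences along with the time effect". For missing data in that model: "Missing values by maximum likelihood will be considered when the MMRM is used". Continuous secondary outcomes that vary over time follow the same method.
- As an addition, a t test or Wilcoxon signed-rank test "will be used to compare results before and after the treatment within each group".
- For the paired t test, the signed-rank test and repeated measures ANOVA: "The last observation carried forward method will be adopted for missing values". Repeated measures ANOVA appears only in this sentence and is assigned to no outcome.
- Testing level: "The significance level will be set at 0.05 in a two-tailed test".

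The Background says that soreness symptoms "usually occur 12–48 h after exercise and mend within 7 days". The Outcome measures section schedules pain scores before exercise and at 0, 1, 6, 12, 24, 36, 48, 60 and 72 h. Table 1 puts the exercise at 0 h and the first dose at 1 h.

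**The concern.** There are two separate weaknesses, both in the additional analyses.

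1. **Before/after tests within a drug.** Every subject exercises and then takes a drug. Pain rises because of the exercise and falls because soreness resolves by itself. A significant change within the JGT periods is therefore expected even if JGT does nothing, and the same change is expected within the placebo periods. The objective is the difference between JGT and placebo, and a within-drug p-value carries no information on it. The choice of the before time is also open, and it can decide whether the test shows worsening or recovery.

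2. **Last observation carried forward (LOCF).** The method assumes that a subject's pain stays at its last recorded value. That is at odds with a course that rises and then resolves. The size and the sign of the error depend on when the subject was last seen.

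At stake is a misleading supplementary result: a within-JGT p-value read as efficacy, or a 72 h mean distorted by carried values. The primary conclusion is not at stake.

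**Working it through.** The protocol gives no figure for dropout, LOCF error or the within-group tests, so there is no stated figure to reproduce. The check uses its design values and assumed soreness curves.

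**Inputs from the protocol.** Thirty men in a 2 × 2 crossover, so up to 30 before/after pairs per drug (Study design); two-sided 0.05 (Statistical analysis); assessment times (Outcome measures).

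**Assumed inputs.** Mean VAS in mm, identical on both drugs (no drug effect):

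| Curve | Pre-exercise | 1 h | 24 h | 72 h |
|---|---|---|---|---|
| Low | 2 | 10 | 28 | 12 |
| Moderate | 2 | 15 | 45 | 22 |
| High | 2 | 25 | 60 | 32 |

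SD and correlation between two times: 20 and 0.5, 25 and 0.3, or 15 and 0.7.

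**Step 1: chance that a before/after test is significant with no drug effect.** The SD of a within-subject change is SD × √(2 × (1 − correlation)). The three settings give 20 × √1.0 = 20.0, 25 × √1.4 = 29.6 and 15 × √0.6 = 11.6 mm. The standardized change is the mean change divided by this SD. The rejection probability comes from the noncentral t distribution with 29 degrees of freedom and noncentrality (standardized change) × √30; the critical value is 2.045.

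Worked case, moderate curve, SD 20, correlation 0.5, 1 h vs 72 h: change 22 − 15 = 7 mm; 7/20 = 0.35; noncentrality 0.35 × 5.48 = 1.92; significant in 46% of trials.

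| Comparison | Change, moderate curve | Significant, moderate curve (SD 20, correlation 0.5) | Range over all curves and settings |
|---|---|---|---|
| Pre-exercise vs 72 h | +20 mm | about 100% | 43–100% |
| 1 h vs 24 h | +30 mm | about 100% | 90–100% |
| 24 h vs 72 h | −23 mm | about 100% | 82–100% |
| 1 h vs 72 h | +7 mm | 46% | 6.5–89% |

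A valid test of the drug would reject in 5%. The choice of times also turns an apparent worsening (+20 mm) into an apparent recovery (−23 mm).

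**Step 2: LOCF error in one treatment's 72 h mean.** Error per dropped subject = mean at the last visit − mean at 72 h. On the moderate curve, last seen at 1 h: 15 − 22 = −7 mm; last seen at 24 h: 45 − 22 = +23 mm. Error in the treatment mean = share dropping out × error per dropped subject. With 10% last seen at 24 h:

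- Low: 0.10 × (28 − 12) = 1.6 mm
- Moderate: 0.10 × (45 − 22) = 2.3 mm
- High: 0.10 × (60 − 32) = 2.8 mm

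**Step 3: what LOCF would do to a JGT–placebo paired contrast at 72 h.** Simulation of 4,000 trials with 30 men, moderate curve, SD 20, within-period correlation 0.6, last visit 24 h and no drug effect:

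| Dropout, JGT vs placebo | Mean difference | Type I error |
|---|---|---|
| None | about 0 | 5.3% |
| 10% vs 10% | about 0 | 5.2% |
| 20% vs 20% | about 0 (−0.2 mm) | 5.1% |
| 0 vs 10% | −2.4 mm | 8.0% |
| 5% vs 20% | −3.4 mm | 12.3% |
| 0 vs 20% | −4.5 mm | 16.9% |

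The error cancels when dropout is equal and becomes an apparent treatment effect when it is not. In the same no-dropout runs, the pre-exercise vs 72 h test was significant in about 100% of trials on both drugs, against 5.3% for the JGT–placebo contrast.

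**The case against.** The strongest defence is one of scope, and most of it stands.

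- **The carry-forward rule is limited to named tests.** The primary outcome and the time-varying continuous secondary outcomes use the mixed model with maximum likelihood. A reader might infer that LOCF biases the trial's main result; the text does not support that. A different missing-data rule for supplementary tests is not in itself a contradiction either.
- **No JGT–placebo test with LOCF is clearly assigned to an outcome.** The paired tests are described as within group, and repeated measures ANOVA is attached to nothing. Step 3 is therefore conditional: it shows what would follow if such a comparison were made. It also keeps a dropped subject's other period, whereas the Intervention section removes a subject who takes or needs medication from the trial, so a man lost in the first stay would have no second value to pair. The same rule is a route by which dropout could depend on pain, but the documents give no sign that it will differ by drug.
- **The before time need not be pre-exercise.** The wording refers to the treatment, and the first dose comes an hour after the exercise entry in Table 1. A reader might assume that pre-exercise is compared with post-exercise; the text does not fix this. With 1 h as the start, the false signal ranges from 6.5% to 89% and is not near certain. The tests may also be meant partly for the safety blood tests, to which the soreness curve does not apply.
- **Dropout in a 4-day inpatient stay may be low**, so the LOCF effect may be small in practice.
- **The protocol nowhere says that within-group p-values will be taken as evidence of efficacy.**

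What remains is that both choices are written into the plan, that neither fits the course of soreness described in the Background, and that the before/after problem needs no missing data at all.

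**Conclusion.** The point holds for the additional analyses only. Within-drug before/after tests on pain cannot show an effect of JGT. Under the assumed curves with no drug effect they are significant in 82–100% of trials for 24 h vs 72 h, 43–100% for pre-exercise vs 72 h and 6.5–89% for 1 h vs 72 h, and the plan leaves the before time undefined. LOCF rests on a flat course that the Background contradicts. Its likely size is modest: 1.6–2.8 mm in a treatment's 72 h mean for 10% dropout after 24 h, with the sign depending on when subjects were last seen, and a bias between drugs only if dropout differs by drug.

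The curve heights, SDs, correlations and dropout rates are assumptions, because the protocol gives none. The direction of the argument does not depend on them; the percentages and millimetres do. The primary mixed model and the time-varying continuous secondary outcomes are not affected.

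**What to change.** In the Statistical analysis section:

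1. Delete the LOCF sentence. Use the likelihood-based mixed model already specified for all repeated continuous outcomes, including any for which repeated measures ANOVA was intended.
2. Replace the within-group before/after tests by the within-subject JGT–placebo difference at the relevant time, and name that time.
3. Report changes within each drug as means with 95% confidence intervals and no p-value. This agrees with the section's existing rule for presenting continuous data.

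The cost is a small change in analysis wording and programming. No visit, measurement or sample size changes.

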### Blinding

The statistician will send the randomization code to the pharmaceutical company for packing to maintain blindness in both the assessors and the subjects. JGT and the placebo drug will be manufactured by the same pharmaceutical company. The placebo drug will be manufactured in a form similar to that of the JGT. It was confirmed in advance that the taste and flavor will be similar. According to the random sequence, the drugs will be packed in the same form and will be delivered to the hospital. The pharmacist will supply the drug sequentially during the trial period, according to the randomization code. The blinding will be maintained until all 30 subjects have completed the study and the database is locked. To evaluate whether the blinding was successful, a quick questionnaire will be conducted at the end of each hospitalization, asking “Which test drug do you think you were allocated to, JGT or placebo drug? And why do you think so?”

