#### Safety assessment

Blood pressure and heart rate will be measured every day using an automated device. In addition, blood tests will be conducted before and after the drug intervention during each hospitalization. The blood tests will include aspartate aminotransferase, alanine aminotransferase, alkaline phosphatase, total bilirubin, gamma-glutamyl transpeptidase, protein, albumin, blood urea nitrogen, creatinine, red blood cells, hematocrit, hemoglobin, white blood cells, and lipids.

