The incidence of serious adverse events (SAEs) and adverse events (AEs) related to the treatment will be analyzed for the safety assessment using the independent *t* test or Wilcoxon’s rank-sum test. The percentage of subjects who experienced one or more side effects during the study will be analyzed using Pearson’s chi-squared test or Fisher’s exact test.

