### Adverse events

During the hospitalization, subjects will be asked if they have any physical discomfort other than DOMS symptoms. Occurrence of any AEs will be recorded on the eCRF after assessing severity and causality. If a SAE occurs, it will be reported to the IRB as soon as possible. If suspected unexpected serious adverse reactions occur, they will also be reported to the Ministry of Food and Drug Safety according to the relevant regulations.

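### The clearly worded adverse event comparison is limited to events judged related to treatment, so drug-caused events blamed on the exercise may be left out of it

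*Protocol article*

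**What the plan says.** The last paragraph of Statistical analysis in the protocol article gives two safety comparisons. The first reads: "The incidence of serious adverse events (SAEs) and adverse events (AEs) related to the treatment will be analyzed for the safety assessment". The second reads: "The percentage of subjects who experienced one or more side effects during the study will be analyzed". The term side effects is not defined, and no causality condition is attached to it.

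The Adverse events section describes collection. During each stay, "subjects will be asked if they have any physical discomfort other than DOMS symptoms". Then: "Occurrence of any AEs will be recorded on the eCRF after assessing severity and causality". All AEs are therefore captured, not only those judged related.

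Three other statements bear on the point:
- Study design: in each stay, "the subjects will perform eccentric exercise for 1 h to induce DOMS". Table 1 puts the first dose 1 h after exercise.
- Blinding: measures are taken "to maintain blindness in both the assessors and the subjects", so causality is judged without knowledge of the drug.
- Safety assessment: "Blood pressure and heart rate will be measured every day using an automated device", and "blood tests will be conducted before and after the drug intervention during each hospitalization".

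**The concern.** The Background makes safety as well as effectiveness something this trial is to demonstrate. The plan collects all AEs, labels each one by opinion, and then compares a labelled subset. Exercise just before dosing offers a ready alternative explanation for a complaint other than DOMS, so a drug-caused event may be labelled unrelated.

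The crossover gives each subject a placebo stay with the same exercise on the same ward. Comparing all AEs between the two stays separates drug from exercise without a causality call on any single event. Filtering on individual opinion first gives up part of that advantage. At stake is a safety statement that rests on the accuracy of attribution, which the document neither gives nor can verify. This concerns which events are counted, whichever test is then applied.

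**Working it through.** **Text check.** The plan's safety elements, side by side:

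| Element | Limited to related events? |
|---|---|
| Recording of AEs (Adverse events) | No, any AE |
| Incidence test, AEs (Statistical analysis) | Yes, as written |
| Incidence test, SAEs (same sentence) | Unclear; the qualifier may attach to AEs only |
| Percentage with side effects (Statistical analysis) | Unclear; term undefined |
| Blood pressure, heart rate, blood tests (Safety assessment) | No |

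The only AE comparison with clear wording is the restricted one.

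**Size.** The document gives no AE rate, no safety power and no attribution rate, so there is no plan figure to reproduce. What follows is an illustration.

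From the document: 30 subjects, each receiving both drugs; two-sided 5% level.

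Assumed: per-stay AE risk of 10% on placebo (background) and 40% on JGT, so 30 percentage points are drug-caused; all 30 subjects complete; responses in the two stays are independent. Let s be the share of drug-caused events judged related, and f the share of background events judged related.

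*Drug-caused events lost* = 30 × 0.30 × (1 − s). This is 0 at s = 1, 2.25 at s = 0.75, 4.5 at s = 0.5 and 6.75 at s = 0.25.

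*Power.* The rates entering the comparison are J = 0.30s + 0.10f on JGT and P = 0.10f on placebo. The discordant probabilities are J(1 − P) and P(1 − J). Power is the exact probability that a two-sided exact McNemar test reaches p ≤ 0.05 with n = 30.

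Counting all AEs means s = f = 1: J = 0.40, P = 0.10, discordant probabilities 0.40 × 0.90 = 0.36 and 0.10 × 0.60 = 0.06. Power is 68%.

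Counting related AEs only:

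| s | f = 0 | f = 0.25 | f = 0.5 |
|---|---|---|---|
| 1 | 92% | 84% | 78% |
| 0.75 | 70% | 60% | 53% |
| 0.5 | 29% | 27% | 25% |
| 0.25 | 2% | 4% | 5% |

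A check by hand for f = 0: every discordant pair favours placebo, and the smallest significant count is 6 (2 × 0.5⁶ = 0.031; 5 pairs give 0.0625). At s = 0.5, J = 0.15 and the chance of 6 or more in 30 is 29%. At s = 1, J = 0.30 and the chance is 92%.

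So the filter raises power when attribution is accurate, roughly breaks even or loses some at s = 0.75, and cuts power heavily at s = 0.5 or below. The all-AE figure does not depend on s or f.

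**The case against.** A reader might infer that the plan counts only related events, that an SAE judged unrelated is excluded, that most complaints will be blamed on the exercise, and that drug-caused events therefore drop out. The document does not support any of these as fact.

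- Side effects is undefined and could mean any AE, in which case an all-AE comparison is already intended.
- The relatedness qualifier can be read as attaching to AEs only. The Adverse events section also sends SAEs to the IRB without a causality condition.
- Nothing says that most complaints are attributable to exercise, and DOMS symptoms are set aside when subjects are asked about discomfort.
- Blood pressure, heart rate and laboratory values need no causality call, so a change in them would still be seen.
- Attribution is blinded, so the same labelling rule applies under both drugs. If it is accurate, nothing drug-caused is lost and the filter removes noise.
- No data are lost. An all-AE table can still be produced from the eCRF.

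These points stand, and they limit the finding to events that may be left out. They do not remove it. A blinded rule is equal for both drugs but need not be accurate, and drug-caused events arise only under JGT, so any that are mislabelled are lost from that side. Vital signs and laboratory tests do not capture symptoms.

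It can also be said that tabulating AEs by relatedness is commonly left to the full protocol or analysis plan. Here, however, the article states the restriction itself, so it is not a gap left to another document.

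**Conclusion.** The point holds in limited form. The clearly worded AE comparison is restricted to events judged related, the second comparison rests on an undefined term, and the status of SAEs is ambiguous. Drug-caused events other than DOMS may be attributed to the exercise and so may be left out, although the placebo stay allows a comparison that needs no such judgement.

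The size is not knowable from the document. Under the assumed 40% versus 10%, with 30 completers, independent stays and an exact paired test, power is 68% counting all AEs. With at most half of background events judged related, it is 25–29% if half of drug-caused events are judged related and 78–92% if all are. It would be wrong to conclude that the filter must reduce power; it can help or hurt, depending on attribution accuracy. The exact paired test is a yardstick here, not the test the plan names.

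The reason to change is that a safety conclusion should not depend on an unverifiable rate when the randomised control and the recorded data make that unnecessary. It should be changed because the remedy is cheap, not because harm is shown.

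**What to change.** In the safety paragraph of Statistical analysis:
- Make the main safety comparison all treatment-emergent AEs and all SAEs, regardless of causality, each assigned to the drug of the stay in which it began.
- Show events judged related as a secondary table.
- Replace the percentage of subjects with side effects during the study by the percentage with at least one AE in each drug's stay.

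The first change also settles whether relatedness applies to SAEs. No new data are needed, because the Adverse events section already has every AE recorded. The cost is a change of wording, one more table, and higher reported event rates under both drugs, since complaints due to the exercise will be included.

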### Randomization and allocation concealment

Subjects will be randomly allocated to either the JGT or the placebo group with equal probability. An independent statistician will use SAS version 9.4 software (SAS Institute, Cary, NC, USA) to generate a random allocation list and will send the list to the pharmaceutical company for packing. The random allocation list will assign 30 subjects to group A or B. According to the crossover design, both groups will take JGT and the placebo drug. Subjects in group A will take JGT and those in group B will take the placebo drug during their first hospitalization.

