## Discussion

This is a protocol for a randomized, double-blind, placebo-controlled, crossover-designed clinical trial to study the efficacy and safety of the herbal medicine JGT in the relief of DOMS in healthy male adults. The strength of this study lies in the rigorous design. In general, DOMS is difficult to test in a clinical trial because of the short duration of the symptoms. A standardized method for pain induction and a rigorously designed clinical trial will provide reliable results on the therapeutic effects of JGT in DOMS. The Standard Protocol Items: Recommendations for Interventional Trials (SPIRIT) checklist is attached as Additional file 1. This study will provide a better understanding of the mechanisms of JGT for relieving muscle pain in general, as DOMS is an important experimental model to evaluate analgesic efficacy and to study movement-related pain [40, 41]. We expect to provide novel insights into potential biological mechanisms of JGT through a metabolomics approach. In this protocol, the inclusion criteria of the study participants will be narrowed to male adults, and participants will be hospitalized during the intervention. Therefore, the results of the metabolomics analysis are expected to yield reliable results, because factors affecting metabolites, such as age, gender, and food intake, will be controlled [42, 43]. Moreover, as this is a 2 × 2 crossover design study, each subject will serve as his own control to reduce individual variations.

To our knowledge, no clinical trial has evaluated the therapeutic effects of JGT on exercise-induced muscle pain. Several clinical trials have evaluated the antispasmodic and analgesic effects of JGT. Clinical trials of JGT to reduce pain have mostly considered pain caused by complications, such as muscular cramps of patients on hemodialysis and myalgia caused by chemotherapy [44–48]. Although it is widely prescribed to manage muscle soreness and myalgia, it is difficult to find any evidence other than a clinical study about JGT on painful muscle cramps in patients with lumbar spinal stenosis [49]. A retrospective case series study with 37 patients treated with JGT for muscle spasms and pain was published in 2004 [16]. However, the current clinical trial will be the first to assess the effect of JGT on exercise-induced muscle soreness. This study will provide valuable data to determine the clinical effects of JGT on exercise-induced pain.

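### Adverse events are to be compared with independent-sample tests although the same 30 men take both drugs; the comparison needs a paired method

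*Protocol article*

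**What the plan says.** The Randomization section of the protocol article states that "The random allocation list will assign 30 subjects to group A or B", and continues: "According to the crossover design, both groups will take JGT and the placebo drug". The Discussion counts this as a strength: "as this is a 2 × 2 crossover design study, each subject will serve as his own control to reduce individual variations". Adverse events are checked repeatedly within each hospitalization (Table 1 and the Adverse events section), so each man's event status is known under each drug.

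The safety paragraph of the Statistical analysis section then reads: "The incidence of serious adverse events (SAEs) and adverse events (AEs) related to the treatment will be analyzed for the safety assessment using the independent", the sentence going on to name the t test, with Wilcoxon's rank-sum test as the alternative. The percentage of subjects with at least one side effect "will be analyzed using Pearson’s chi-squared test or Fisher’s exact test". For categorical data in general, the same section says: "Categorical data will be analyzed using the chi-squared test or Fisher’s exact test". The level is fixed as follows: "The significance level will be set at 0.05 in a two-tailed test".

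Paired tests are named only for before-and-after comparisons within a group. The primary repeated-measures model does include subject as a random factor.

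**The concern.** The independent t, rank-sum, chi-squared and Fisher tests all treat the two samples as different people. Here a JGT-versus-placebo comparison would count 30 men as 60 independent persons. A man who readily reports discomfort is likely to do so in both hospitalizations. The difference between drugs then varies less than these tests suppose, and their p-values are too large.

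For efficacy, a conservative test costs power. For harms, it also invites a reader to take a non-significant result as reassurance. The Background section says that the safety of JGT will be demonstrated, so the comparison matters even though it is a supporting one.

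**Working it through.** **Inputs.** From the protocol article: 30 men, both drugs in each man, two-sided 0.05. The article gives no adverse event rate and no within-subject correlation ρ. Both are assumptions below and are shown over a range. The article states no figure for this comparison, so there is none to reproduce first.

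**1. Which comparison is meant?** There are two readings of the safety paragraph.
- JGT exposures against placebo exposures: the two samples are the same 30 men, so the independence assumption fails.
- Events pooled over the whole study, group A against group B: both groups took both drugs, so the test compares sequences and says nothing about JGT versus placebo.

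Independent-sample tests on within-subject period differences would be valid in a crossover, but the text speaks of incidence and percentages of subjects, not of such differences.

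**2. Continuous or count data, large-sample.** The unpaired test uses variance 2σ²/n for the difference in means; the true variance is 2σ²(1−ρ)/n. The true level is therefore about 2[1−Φ(1.96/√(1−ρ))]:
- ρ = 0.3: 1.96/√0.7 = 2.34, level 1.9%
- ρ = 0.5: 1.96/√0.5 = 2.77, level 0.6%
- ρ = −0.2: 1.96/√1.2 = 1.79, level 7.4%

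Simulation of the independent t test with 30 pairs of normal values gives 2.0%, 0.7% and 7.1%; the paired t test stays near 5%.

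**3. Subjects with at least one event: exact level.** Let the rate be p = 20% under both drugs. The probability of an event on both is p² + ρp(1−p) = 0.04 + 0.16ρ. The probability of an event on one given drug only is 0.16(1−ρ), which is 0.112 at ρ = 0.3 and 0.080 at ρ = 0.5. Enumerating all outcomes for 30 men at nominal 0.05 (chi-squared without continuity correction):

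| ρ | chi-squared | Fisher | exact McNemar | mid-p McNemar |
|---|---|---|---|---|
| 0.3 | 2.03% | 0.66% | 1.53% | 3.47% |
| 0.5 | 0.72% | 0.16% | 0.80% | 2.35% |

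**4. Power.** Assume 30% on JGT and 10% on placebo. The probability of an event on both is 0.03 + ρ√(0.21 × 0.09) = 0.03 + 0.1375ρ, and the enumeration is the same:

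| ρ | chi-squared | Fisher | exact McNemar | mid-p McNemar |
|---|---|---|---|---|
| 0.2 | 50% | 35% | 42% | 54% |
| 0.4 | 50% | 33% | 51% | 66% |

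**5. What one result would look like.** Suppose 10/30 men report on JGT and 4/30 on placebo. The unpaired tests see only these totals. Chi-squared: z = (6/30)/√(0.2333 × 0.7667 × 2/30) = 1.83, p = 0.067. Fisher: p = 0.125. The paired answer depends on how many men k report on both drugs. The discordant counts are 10−k and 4−k, and exact McNemar p is twice the lower binomial tail:

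| k | discordant | exact McNemar p |
|---|---|---|
| 0 | 10 v 4 | 2 × 1471/16384 = 0.18 |
| 1 | 9 v 3 | 2 × 299/4096 = 0.15 |
| 2 | 8 v 2 | 2 × 56/1024 = 0.11 |
| 3 | 7 v 1 | 2 × 9/256 = 0.07 |
| 4 | 6 v 0 | 2 × 1/64 = 0.03 |

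The same totals thus carry different evidence, which the planned tests cannot see.

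**The case against.** The strongest reply is that correcting the test changes little in practice. Much of that stands.
- In step 5, exact McNemar falls below 0.05 only at the greatest possible overlap. For k = 0 to 3 its p-value is larger than that of chi-squared, and for k = 0 or 1 also larger than that of Fisher. A reader might infer that a paired test would reveal a harm the planned test hides; that holds only if the events cluster in the same men.
- Exact McNemar is itself conservative with 30 men, and it can have less power than chi-squared: at assumed rates of 20% v 5% and ρ = 0.2, 27% against 44%. At a 10% event rate even mid-p McNemar has a true level of only 1.5% at ρ = 0.3 and 0.6% at ρ = 0.5. With rare events no test on 30 men will say much.
- Apart from adverse events, the outcomes are almost all numeric. The treatment guess in the blinding questionnaire is the only other evident categorical item, so a claim of wide damage to categorical outcomes is not supported.

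A reader might also infer that only events judged related to treatment will be compared. The text does not settle this: any adverse event is recorded, and the percentage of subjects with side effects is analyzed separately.

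None of this makes the planned tests suitable. Nor can the matter be left to an unseen analysis plan, because the article itself names the tests.

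**Conclusion.** Wrong as written. The tests named for adverse events do not fit a design in which each man takes both drugs, and no reading of the paragraph repairs that. Under assumed positive within-subject correlation they are generally too conservative: at a 20% event rate the true level is about 0.7% to 2.0% for chi-squared and 0.2% to 0.7% for Fisher, over ρ from 0.5 to 0.3. With negative correlation the t test is too liberal (7.1% at ρ = −0.2). Rates and correlations are assumptions throughout.

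It should be fixed, but it is not a critical fault. A reader might infer that the efficacy conclusion is compromised. The document does not support that: the primary VAS model carries subject as a random factor, and the continuous secondary outcomes measured over time follow the same method. Nor, under positive correlation, are false alarms inflated.

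**What to change.** In the safety paragraph of the Statistical analysis section:
- Attribute each adverse event to the drug of the period in which it occurs.
- Compare subjects with at least one event by one named paired method: McNemar, preferably mid-p because the exact version is itself conservative with 30 men, or Mainland-Gart if period is to be allowed for.
- Report the paired risk difference with its 95% CI.
- Compare event counts per subject by the signed-rank test in place of the independent t or rank-sum test.
- Amend the general sentence on categorical data so that any comparison of the two drugs within the same men is paired.

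This changes analysis wording only. It needs no new data and no more subjects, because event status is already recorded in each hospitalization.
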